##### (d) Clinical measures

- LDL-C (Low-density lipoprotein-Cholesterol)
- Total Cholesterol
- Triglycerides
- HDL-C (High-density lipoprotein-Cholesterol)
- HbA1c (Glycosylated haemoglobin, type A1C)
- Serum creatinine
- Estimated Glomerular filtration rate (eGFR)
- Urine albumin to creatinine ratio (ACR)
- Height
- Weight
- Blood pressure

#### 2. Secondary exposures:

##### (a) Life events

- Pregnancy (defined by 3rd trimester delivery – live birth or stillbirth)
- Hypertensive disorders of pregnancy
- Gestational diabetes
- Menopause
- Lives in a care home
- Date and cause of death

[figure not shown]

*(b) Health service utilisation*

- Number of hospital admissions per year
- Number of primary care consultations per year

A code set has been built for all multimorbidity conditions by comparing published code sets from previous studies (2,3) and those built by CPRD for use with their GOLD data. All code sets are being clinically revised using CPRD GOLD code browser.

Considering that CPRD GOLD and Aurum have different structures, in order to use the same codes we plan to map the code sets by matching the Read codes and dm +d codes across CPRD GOLD and Aurum medical and product dictionaries to identify the same set of conditions and prescribing, respectively.

## N. Data/ Statistical Analysis

### Research Aim A)

We will estimate the prevalence of each condition included in our consensus-built list of 220 conditions across sex, age groups and ethnic groups (White, Black African and Caribbean, and south Asian). We will also describe the presence of multimorbidity ( $\geq 2$  conditions) across different sociodemographic characteristics (age, sex, ethnic groups and deprivation level).

We intend to apply unsupervised machine learning techniques to identify clusters of multimorbidity across an unselected population, and within specific ethnic groups. Recent research suggests that unsupervised learning techniques have potential to identify novel patterns and relationships from electronic health records and reveal latent disease clusters and patient subgroups (16). We will potentially use the overlapping technique, which allows each disease to belong to two or more clusters that present separate degrees of membership. The advantage of using this type of clustering is that the diseases on the boundaries between several clusters are not forced to fully belong to a single cluster, but rather are assigned membership degrees between 0 and 1 indicating their partial membership (17,18). We may apply a prevalence-based revision of the conditions included in our multimorbidity clusters (as used by Kuan and colleagues (2) who set a prevalence cut off of 0.01% in their data-driven analysis) if there is concern that very low prevalence conditions are subject to reporting bias or poor data quality.

We will describe the patterns of multimorbidity by calculating the frequencies and percentages of conditions within each cluster, and diseases will be assigned to the cluster in which they present the highest membership value. The membership value will be estimated using the ratio between the disease prevalence within the cluster by the disease prevalence in the overall population (19). We will examine how clustering varies in the context of more prevalent conditions (e.g. diabetes, hypertension, depression) compared to less prevalent conditions (e.g. HIV and cancer).

We will use the CPRD Aurum as a validation data set, aiming to replicate our methods and validate our findings in an ethnically-diverse East London population.

### Research Aims B)

To characterise the trajectory of multimorbidity clusters across the life course, we will identify clusters of multimorbidity and trace their evolution from single index conditions, and their trajectories across the lifecourse, including to death, over ten years. We anticipate focusing this analysis on up to 8 multimorbidity clusters, selected to ensure we generate new knowledge, e.g. clusters which include less-studied conditions such as cancer or HIV, as well as those where there is variation by ethnicity. We will follow the individuals within the selected clusters to identify the acquisition of new conditions and potentially changes in the cluster they belong to over time. Our analysis will consider how these trajectories to multimorbidity vary according to different 'index conditions', e.g. diabetes, HIV and cancer.

The assessment of the sequence of multimorbidity clusters an individual belongs to over the years will allow us to understand their disease trajectory over the period they were under observation and at different points in time. The multimorbidity cluster trajectories assessment will take into account the individuals' socioeconomic characteristics, potential risk factors and time dependent variables (e.g. clinical measurements, health seeking behaviours, health care utilisation, and life events).

[figure not shown]

We will identify individuals who share similar patterns of multimorbidity using clustering algorithms at different points in time. We aim to assess at least three points in time, with a ~five year interval between them (e.g. Jan 2011, Jan 2016 and Dec 2020). This time window will be subject to revision according to the available follow-up time in years of our study population. To evaluate the multimorbidity cluster trajectories, each individual will be assigned to the cluster with the highest membership degree in each point in time. We will be able to identify how the multimorbidity cluster changes in individuals from different age groups, sex and ethnicity.

We will estimate the association between the multimorbidity clusters and the risk to mortality in each follow-up period using Cox models adjusted by socioeconomic characteristics (age, sex, IMD) and risk factors (clinical measurements, health seeking/risk behaviours, health care utilisation, and life events) some of which are time dependent variables (e.g. BMI, blood pressure, lipids, HbA1c).

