### Research Aims B and C)

Our research aims B and C will assess the trajectories of multimorbidity clusters of diseases and their relationship with prescribing. The main outcome of this analysis is the change of cluster the patients belong to over time. We will also consider mortality (date and cause of death) as a secondary outcome of the observational cohort. We will evaluate whether the progression of multimorbidity trajectories is predicted by known risk factors (e.g. high socioeconomic deprivation, smoking status, body mass index and clinical measures), and how it varies across different ethnic groups (White, Black African and Caribbean, and south Asian). Additionally, we have selected some indicators of health-seeking/risk behaviours, health care utilisation and life course variables. These variables are as follows:

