### P. Plans for addressing missing data

We will assume that the individuals who do not have any recorded code do not have the disease (for further discussion, please also see Section T. Limitations on the study design). We will include patients who have complete data for the stratification variables (e.g. sex, age and ethnic groups) and who have linked measures of deprivation. Given the high levels of missingness for some covariates, i.e. body mass index, total cholesterol, and alcohol intake specific statistical techniques will be applied to handle missing-not-at-random data, e.g. sensitivity analysis and multiple imputation techniques where appropriate.

The design of the study assumes that patients who do not meet the criteria according to the coding algorithm do not have the disease. This may introduce biases due to under-reporting or misreporting. Please see section O for further details.

In the main analyses, where patients will be stratified by age and sex, any individuals with missing data for either will be excluded. In addition, patients without data for ethnicity and deprivation will be excluded from sensitivity analyses.

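### Admissions and consultations are listed as exposures for cluster progression, but progression is recorded only at those contacts, so an association with utilisation is expected even if contacts are unrelated to disease onset

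*Protocol*

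**What the plan says.** **Outcome.** Section M (Research Aims B and C) states: "The main outcome of this analysis is the change of cluster the patients belong to over time". Section N (Research Aim B) follows individuals to "identify the acquisition of new conditions and potentially changes in the cluster they belong to over time".

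**Exposure.** Section M lists, under secondary exposures (health service utilisation), "Number of hospital admissions per year" and "Number of primary care consultations per year". Its introduction to Aims B and C says "We will evaluate whether the progression of multimorbidity trajectories is predicted by known risk factors", gives deprivation, smoking, body mass index and clinical measures as examples, and then continues: "Additionally, we have selected some indicators of health-seeking/risk behaviours, health care utilisation and life course variables". Section N says the trajectory assessment will take account of "time dependent variables (e.g. clinical measurements, health seeking behaviours, health care utilisation, and life events").

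**Recording rule.** Section P: "We will assume that the individuals who do not have any recorded code do not have the disease".

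**Source.** Section J uses HES admitted-patient care both to find hospital-coded conditions and to count admissions per year.

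**Direction of effect.** The rationale in section D treats healthcare utilisation as something multimorbidity has an impact on, which is the reverse of its role in the section M list.

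**The concern.** A condition can enter the record only at a contact: a consultation for primary care codes, an admission for HES codes. People with more contacts have more chances for an existing condition to be coded, and those with few contacts are counted as free of it. The exposure is then partly the instrument that records the outcome. Causation also runs backwards, because a new diagnosis brings follow-up visits and admissions. With cluster assessments about five years apart, a count taken over the same interval would mix contacts before, at and after the diagnosis.

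At stake is the Aim B statement of what predicts progression. Utilisation could appear as a determinant without being one. In a dataset of about 3 million patients (section I), even a small artefact would be statistically clear. The study is hypothesis-generating, but section J expects its findings to support care stratification and prevention, so a hypothesis produced by the recording process has a cost.

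**Working it through.** **1. The plan's own figure.** The protocol gives no figure on this point. Its one computed design figure is the prevalence sample size: 1.96² × 0.272 × 0.728 / 0.002² = 190,174.6, which reproduces the stated 190,174. It does not bear on this issue.

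**2. Is the mechanism addressed anywhere?** Section P admits that the no-code rule may bias results through under-reporting or misreporting and refers to section O. Section O describes only stratification by sex, age group and ethnic group. Section T mentions unrecorded, miscoded and undiagnosed disease, and weaker recording of non-incentivised conditions. It does not say that recording depends on contact frequency.

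**3. Expected artefact under no effect (closed form).** All rates here are assumptions; none is in the protocol. True onset hazard λ = 0.10 per year, independent of contacts; T = 5 years; r contacts per year; each contact codes an existing condition with probability q, so the detection hazard is μ = rq. The probability of being coded within T is

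P = 1 − [μ·e^(−λT) − λ·e^(−μT)] / (μ − λ).

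True five-year risk in every group: 1 − e^(−0.5) = 39.3%.

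Example, q = 0.05:
- r = 10, μ = 0.5: 1 − (0.5 × 0.6065 − 0.1 × 0.0821)/0.4 = 26.2%
- r = 1.5, μ = 0.075: 1 − (0.075 × 0.6065 − 0.1 × 0.6873)/(−0.025) = 7.0%
- risk ratio 3.7; true value 1

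| q | coded risk, r = 1.5 | coded risk, r = 10 | risk ratio |
|---|---|---|---|
| 0.05 | 7.0% | 26.2% | 3.7 |
| 0.10 | 12.5% | 32.7% | 2.6 |
| 0.25 | 22.9% | 36.8% | 1.6 |
| 0.50 | 30.4% | 38.1% | 1.25 |

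The ratio shrinks as coding becomes more complete but stays above 1 throughout.

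**4. Does lagging cure it?** Person-year simulation: 200,000 people, five years, same λ, contact rates gamma-distributed between people (mean 5 per year, shape 1). Rate ratio of newly coded disease, 8 or more versus 1 or fewer contacts:

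| q | contacts in same year | contacts in prior year |
|---|---|---|
| 0.05 | 14.3 | 4.8 |
| 0.10 | 9.5 | 3.2 |
| 0.25 | 4.8 | 2.0 |
| 0.50 | 2.8 | 1.5 |

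The ratio for true onset was 0.99 to 1.01. A one-year lag reduces the artefact but does not remove it, because frequent attenders in one year tend to be frequent attenders in the next.

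**5. Effect on other determinants.** Assume a group with no true difference in onset but fewer contacts (3.5 versus 5 per year) and 30% coding per contact. Under detection bias alone, the unadjusted odds ratio for the group was 0.91, and adjustment for same-interval contacts brought it to 0.99, closer to the true value of 1. With 4 extra contacts after diagnosis and same-interval measurement, adjustment overshot to about 1.26 to 1.36. A second simulation, with the 4 extra contacts spread over the whole five years, gave 1.06 to 1.20. The direction is the same in both; the size depends on how the contacts enter.

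**The case against.** The strongest reply is that the protocol does not state the analysis being criticised. Section N names no progression model and no measurement window. Its only specified regression is a Cox model for mortality, where utilisation is an adjuster and the outcome does not depend on GP coding. The sentence about prediction gives other examples, and utilisation comes in a separate sentence. The secondary exposure list also contains date and cause of death, which section M elsewhere calls an outcome, so the heading is partly a variable list. Windows and lags are commonly left to an analysis plan.

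Much of this stands. A reader might infer that the protocol commits to same-interval counts, or that it is certain to report utilisation as a determinant; the text supports neither. A reader might also infer that the ethnicity, deprivation and smoking estimates will be distorted. That is only conditional: it could happen if same-interval counts are adjusted for and diagnosis raises contacts, whereas under detection bias alone adjustment may help. Nor should one take from the extreme case, a condition coded only at admission and so never recorded in people not admitted, any measure of size: that holds by construction, and the protocol also uses primary care codes.

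What does not fall away is the role the protocol gives utilisation. It is labelled an exposure, placed among the time-dependent variables for trajectories, and set against an outcome recorded at the same contacts. No choice of model changes that, and the general remarks on misclassification do not cover it.

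**Conclusion.** The point holds as a problem of role and interpretation. Under the stated recording rule, an association between utilisation and recorded progression is expected without any effect on onset, and reverse causation adds to it. The direction was away from the null in every scenario tried.

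The size is not a property of this protocol. The five-year risk ratio of about 1.25 to 3.7 rests on assumed onset, contact and coding rates and concerns any one newly coded condition. Change of cluster, which a new code need not cause, was not modelled.

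A reader might extend the argument to clinical measures that help make a diagnosis, such as HbA1c for diabetes or blood pressure for hypertension. That is a reasonable secondary caution when interpreting transitions defined by those conditions, but no calculation was done and the documents do not show it to be an error.

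**What to change.** For the cluster-progression analysis, in section M (Research Aims B and C and the secondary exposure list) and section N (Research Aim B):

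1. State that utilisation will not be interpreted as a determinant of progression. Report it as a descriptor or consequence of clusters, in line with section D, or use it as an ascertainment variable.
2. Where it is used to stratify or adjust, measure it in a fixed window that ends before the interval at risk (for example the preceding 12 months), and report the other determinants with and without it.
3. In section T, state that recording depends on contact frequency and that lagging reduces but does not remove the resulting bias. Correct section P's reference to section O: the relevant discussion is in section T, which section P's opening sentence already cites.

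The cost is wording and variable derivation from data already requested. The downsides are that lagged counts are less current, some patients will have no data in the window, and utilisation is no longer reported as a determinant.

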#### C. Outcomes to be Measured

**Primary outcome(s):**

[figure not shown]

- (a) The clusters of multimorbidity\*; and,
- (b) The multimorbidity cluster trajectories throughout the follow up period.

\*Multimorbidity will be defined as the presence of two or more long-term conditions (out of the clinical consensus-derived 220 conditions described in appendix 1) within the same individual. Unsupervised machine learning algorithms applied to the dataset will then derive and define clusters of multimorbidity, by grouping similar entities together (using an understanding of difference in distance between data points). A sample of code sets used to select conditions are shown in Appendix 2.

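### Nothing holds the cluster definitions constant across dates, so a change of cluster can be counted in people whose conditions have not changed

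*Protocol*

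**What the plan says.** All references are to the protocol.

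- Section C, primary outcome (b): "The multimorbidity cluster trajectories throughout the follow up period".
- Section M, Research Aims B and C: "The main outcome of this analysis is the change of cluster the patients belong to over time".
- Section N, Research Aim B, on how the groups are formed: "We will identify individuals who share similar patterns of multimorbidity using clustering algorithms at different points in time".
- The same section, on timing: "We aim to assess at least three points in time, with a ~five year interval between them". The dates given are examples and may be revised.
- The same section, on assignment: "each individual will be assigned to the cluster with the highest membership degree in each point in time".
- The same section, on scope: "We anticipate focusing this analysis on up to 8 multimorbidity clusters". Section B places this selection after the cross-sectional clustering of Aim A.
- The same section, on follow-up: "We will follow the individuals within the selected clusters to identify the acquisition of new conditions and potentially changes in the cluster" to which they belong.
- Section N, Research Aim A, on membership of diseases in clusters: "The membership value will be estimated using the ratio between the disease prevalence within the cluster by the disease prevalence in the overall population".

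The protocol does not say that one cluster solution is kept for all dates, how clusters found at different dates correspond, or that a transition requires a new condition. Section T accepts that the solution depends on which conditions are included. It does not mention dependence on the date of fitting.

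**The concern.** A change of cluster is informative about a person only if the clusters mean the same thing at both dates. When an unsupervised model is fitted again at a later date, a person's assignment depends on the disease pattern of everyone in the data at that date as well as on the person's own conditions. Over five years the population accrues conditions, and cluster centres and boundaries move. Someone close to a boundary can then be reassigned with no change in health. Taking only the highest membership turns a small shift into a full change of category.

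Two things are at stake. First, primary outcome (b) would combine disease progression with movement of the definitions. Section N promises to show how clusters change by age group, sex and ethnicity, and those comparisons could not separate the two. Second, the plan selects up to 8 clusters for follow-up and carries them into Aim C. If later fits are free, nothing ensures that those clusters are found again.

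**Working it through.** **Plan's own figure.** The protocol gives no figure for transitions. Its one calculated sample size concerns prevalence (Section I) and reproduces: 1.96² × 0.272 × 0.728 / 0.002² = 190,174.57, against 190,174 stated. It does not bear on this point.

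**Step 1: what assignment depends on.** Let x be a person's set of conditions and m(k,t) the centre of cluster k fitted at date t. Highest-membership assignment at date t is c(t) = the k for which x is closest to m(k,t).

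- One fixed solution: m(k,t) = m(k) at every date. If x is the same at two dates, c is the same. The share of unchanged people who move is exactly 0.
- Refitting: m(k,t) varies with t. The same x can be closest to a different centre at the second date, so c can change.

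The Aim A membership ratio also depends on the population, because both its numerator and its denominator are prevalences in the data analysed. It is defined for diseases, not persons. At least three dates give at least two intervals in which such a change can occur.

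**Step 2: label matching.** Separate fits number their clusters arbitrarily. Without a rule to pair them, change of cluster is not defined. The protocol states no such rule.

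**Step 3: illustration of size.** The protocol supplies no inputs for this, so every setting below is an assumption. Both simulations use two dates and 30 binary conditions. The results are the share of people with identical conditions at both dates who were assigned to a different cluster.

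| Setting | Refitted, labels optimally matched | One fixed definition |
|---|---|---|
| k-means, 6 clusters, 20,000 people, about 70% unchanged, 12 runs | median 41% (16% to 55%) | 0% |
| Fuzzy c-means, 6 clusters, 15,000 people, 8 runs | mean 21% (3% to 31%) | 0% |
| Fuzzy c-means, 8 clusters, 15,000 people, 8 runs | mean 22% (7% to 46%) | 0% |

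Further results from the fuzzy c-means runs (fuzzifier 1.2, best of 4 starts, conditions that only accrue, on average 58% of multimorbid people unchanged):

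- Without label matching, the mean share of unchanged people who moved was 83% with 6 clusters and 85% with 8.
- Labels were matched on the unchanged people themselves, so the matched figures are the lowest that any one-to-one pairing of labels could give for them.
- Refitting the same first-date data from new random starts moved a mean of 1.5% (6 clusters) and 9% (8 clusters). Part of the movement is therefore algorithm noise.
- Among people who did gain conditions, a fixed definition moved a mean of 26% (6 clusters) and 28% (8 clusters). In these settings, the spurious movement of 21% to 22% in unchanged people is of similar order to the real movement in changed people.

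**The case against.** **Refitting is inferred.** The protocol never says that clusters are re-derived. Section B selects clusters first and follows them afterwards, Section N follows people within the selected clusters, and Aim C refers back to the Aim B clusters. This could mean that one solution is applied at several dates. A reader might infer that the protocol explicitly commits to separate fits, and it does not. What stands is that the sentence on clustering at different points in time most naturally describes clustering at each date, and that no passage holds the definitions constant. The passages on selected clusters sharpen the problem, because they need clusters that persist.

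**This is detail for a statistical analysis plan.** Such a plan may exist and may settle the matter. But the protocol itself sets the outcome, the clustering by date and the assignment rule, and as worded these three do not fit together.

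**Evolving clusters are a legitimate target.** They are, particularly in a study designed to generate hypotheses. But the outcome in Section M is change in the cluster that a patient belongs to, which needs a constant definition. The two aims can be met by separate analyses. Section N also tracks new conditions directly, so unchanged people could be identified, but the transition outcome does not use that information.

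**The simulations do not transfer.** This is correct as to size. The protocol has 220 conditions and about 3 million patients, and its algorithm is not settled. Neither simulation modelled ethnicity or death.

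**Deaths.** A reader might also infer that deaths between dates disappear from the trajectories. The documents do not support this. Cluster to death is a secondary outcome (Section C), follow-up runs to death or leaving the database (Section K), and Section N traces trajectories to death and fits Cox models for mortality in each follow-up period.

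**Conclusion.** The point holds on the natural reading of Section N, Research Aim B. With clustering run at each date and no anchor, a person whose conditions are identical at two dates can be counted as a transition in the main outcome of Aims B and C, and the selected clusters need not recur. That conclusion follows from the design and needs no simulation.

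The size is not known. The simulated range of about 3% to 55% shows the mechanism under assumed settings and does not estimate a rate in CPRD. It would be wrong to quote any single figure from it as the expected share of false transitions. Whether the effect differs by age, sex or ethnicity has not been shown; the plan simply gives no means of separating it from true differences. If a single fixed solution is in fact intended, the defect is one of wording. The change should be made, but the point does not invalidate the study.

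**What to change.** In Section N, Research Aim B, replace the sentence on clustering at different points in time with a statement that:

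- the cluster model is derived once, from the Aim A solution or from pooled person-dates (name which);
- that fixed rule is applied to each person's conditions at every date, and person-level change of cluster is defined from these assignments;
- refits at other dates are reported separately, as a stability check and as a description of how the clusters themselves evolve, with the rule for matching clusters stated.

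Sections C and M can then refer to this definition. Showing death and leaving CPRD as end states in the transition tables is optional.

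The cost is a few lines of wording and less computation in the main analysis. The small downside is that clusters emerging only at later dates appear in the secondary analysis and not in the main trajectories.

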#### B. Technical Summary (Max. 300 words)

Our proposal seeks to deliver new knowledge on multimorbidity through the application of hypothesis-generating, data-driven analytical tools to a large-scale electronic health record dataset from a nationally-representative population. We seek to expand on previous multimorbidity research (which focuses predominantly on 30-40 common chronic conditions) to define clusters and trajectories of multimorbidity across ~200 long-term conditions. This large set of conditions have been defined through a rigorous consensus-building process and extensive review of existing validated code sets (including previously-published CPRD studies undertaken by CALIBER and the Cambridge Multimorbidity group (1–3)).

We will initiate our analyses using a cross-sectional design, applying data-driven clustering (unsupervised machine learning) to identify clusters of multimorbidity in England population across our extensively-curated ~ 200 long-term conditions obtained from primary care data and linked Hospital Episode Statistics (HES). We will stratify our analysis by ethnicity to identify how multimorbidity clusters across ethnic groups (including White, Black African and Caribbean, and south Asian).

Subsequent to this hypothesis-generating clustering, we will use an observational cohort design to investigate how multimorbidity clusters develop from index conditions and how they change over time, including to death (using linked Office for National Statistics mortality data). At this point, we will focus on a limited number of multimorbidity clusters (up to 8) selected to ensure we generate new knowledge, e.g. clusters which include less-studied conditions such as cancer or human immunodeficiency virus, as well as those where there is variation by ethnicity. We will then use epidemiological analyses, including Cox model, adjusted by socioeconomic characteristics (age, sex, ethnicity, Index of Multiple Deprivation), and time-dependent variables (e.g. risk factors, clinical measurements) to characterise these trajectories. Additionally, we will apply artificial intelligence techniques (including supervised and unsupervised machine learning) for focused analyses to examine the interrelationship between specific multimorbidity clusters under study and prescribing/polypharmacy patterns.

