### O. Plan for addressing confounding

To address confounding we selected a priori confounders that according to the literature are associated with an increased risk for multimorbidity. The main strategy to address confounding will be the analysis stratification according to sex, age group and ethnic groups (White, Black African and Caribbean, and south Asian).

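### The one mortality Cox model described conditions on service use, life events and time-dependent measures that can follow cluster assignment, so it does not give prognosis by cluster; its covariate lists also need reconciling

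*Protocol*

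**What the plan says.** Section C makes the step from multimorbidity cluster to death a secondary outcome. Section N (Research Aim B) estimates it in each follow-up period with "Cox models adjusted by socioeconomic characteristics (age, sex, IMD) and risk factors (clinical measurements, health seeking/risk behaviours, health care utilisation, and life events", and adds "some of which are time dependent variables (e.g. BMI, blood pressure, lipids, HbA1c". No other mortality model is set out in that section.

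The covariate groups are defined in Section M. Health service utilisation contains "Number of hospital admissions per year" and the matching count of primary care consultations. Life events contain pregnancy-related items, menopause, care-home residence and "Date and cause of death". The same section says of death: "We will also consider mortality (date and cause of death) as a secondary outcome of the observational cohort".

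The Technical Summary (Section B) describes the model as "including Cox model, adjusted by socioeconomic characteristics (age, sex, ethnicity, Index of Multiple Deprivation), and time-dependent variables (e.g. risk factors, clinical measurements", so ethnicity is among the adjusters there. Section O states: "The main strategy to address confounding will be the analysis stratification according to sex, age group and ethnic groups".

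On purpose, Sections G and J say that the clusters and their trajectories should help to pick out patients who are alike in prognosis and in their need for care.

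**The concern.** A clinician or commissioner will read a cluster's mortality hazard ratio as its outlook: how much likelier death is for people in this cluster than for others of the same age, sex and background. That reading needs adjustment for what precedes cluster membership. The planned model also conditions on things that may follow from it. If a cluster raises mortality partly by way of poor glycaemic control, repeated admission or a move to a care home, holding these constant takes that part out of the hazard ratio. What remains answers a different question: the association at equal service use and equal clinical values.

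Two inconsistencies in the text make the model harder to apply as written. Ethnicity is a Cox covariate in one section and not in another, although variation by ethnicity is a central aim. And one covariate group contains the outcome.

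**Working it through.** **1. Timing.** Section N assigns each person to a cluster at three or more time points about five years apart and studies mortality in each follow-up period. A value updated within a period comes after the assignment that opens it. Section N names BMI, blood pressure, lipids and HbA1c as time dependent. For the yearly admission and consultation counts it does not say whether the years lie before or after assignment.

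**2. Content.** Section E expects clusters built around diabetes and hypertension; HbA1c and blood pressure measure those diseases. Section J uses hospital admission records both to find conditions and to count admissions, so admissions help to form the exposure and are then conditioned on. Smoking, BMI or lipids recorded before assignment are different: they can precede cluster membership and confound it.

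**3. Size of the possible attenuation.** The protocol states no hazard ratio, death rate or event count for this model, so there is no figure to reproduce. Its only sample-size formula (Section I) does reproduce, 1.96² × 0.272 × 0.728 / 0.002² = 190,174.6 against 190,174, but it concerns the precision of a prevalence.

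An illustration on wholly assumed inputs: 20,000 people, 30% in the cluster (C = 1), ten years, one pure mediator M = a·C + standard normal noise, and hazard 0.02 × exp(ln 1.5 · C + b·M) per year. The direct hazard ratio is therefore 1.5 by construction.

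| a (SD shift) | b (log-HR per SD) | Cluster HR without M | Cluster HR with M |
|---|---|---|---|
| 0.25 | 0.2 | 1.53 | 1.45 |
| 0.25 | 0.7 | 1.71 | 1.50 |
| 0.5 | 0.4 | 1.77 | 1.49 |
| 1.0 | 0.2 | 1.84 | 1.48 |
| 1.0 | 0.7 | 2.76 | 1.51 |

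Over the full grid of nine settings the ratio without M ran from 1.53 to 2.76, and with M from 1.43 to 1.54, which is scatter around 1.5. On the log scale the loss is 1 − ln 1.45 / ln 1.53 = 13% in the first row and 1 − ln 1.51 / ln 2.76 = 59% in the last. Because M is built as a mediator, this shows what follows if the covariates act that way, not that they do.

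**4. Ethnicity.** Section B lists age, sex, ethnicity and IMD; Section N lists age, sex and IMD. Section O stratifies by ethnic group, but also by age group and sex, which Section N still lists as adjusters. Stratification alone therefore does not explain why ethnicity is absent.

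For scale, take the minority share from Section H, 7.8% + 3.5% = 11.3%. Assume cluster prevalence of 0.4 or 0.6 in that group against 0.3 in the rest, and an ethnicity hazard ratio of 0.7, 0.8 or 1.25. Omitting ethnicity then gave, at the extremes, 1.415 instead of 1.473 (−4%) and 1.542 instead of 1.502 (+3%); the smallest change was about 1%.

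**5. Death among the life events.** Section N adjusts for life events, and the only list under that name, in Section M, includes date and cause of death. Section C and the opening of the Aims B and C text in Section M make death an outcome. In a simulated set of 5,000 with a true cluster log-HR of 0.41, a death indicator as covariate got a coefficient of 31.4 with standard error about 38,000, and the cluster log-HR became −0.13. With date of death as covariate the fit returned no estimates.

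**The case against.** The strongest reply is that the study is descriptive and meant to generate hypotheses (Section F), does not set out to contrast exposed with unexposed patients (Section G), and seeks only an association. An association adjusted for clinical values and service use is a legitimate quantity. Section M treats many of these covariates as known risk factors, and those that precede cluster membership belong in the model. Section N speaks of Cox models in the plural and rules out no simpler one. Covariate timing is often left to a statistical analysis plan, which is not at hand.

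Most of this stands, and it rules out the stronger readings. A reader might infer that the hazard ratios would be wrong; the protocol does not support that, because it claims no total effect and several covariates may be true confounders. A reader might infer that ethnicity is uncontrolled; Section B includes it and Section O stratifies by it, so this is an inconsistency. A reader might infer that death would be entered as a predictor of itself; the outcome statements in Sections C and M point to a misplaced line in a list, and the literal model fails too visibly to pass unnoticed.

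The reply does not remove the mismatch of purpose. Prognosis by cluster is what Sections G and J want, and the only model described conditions on service use and time-dependent values without labelling the result as conditional.

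**Conclusion.** The point holds as a limited one. The sole mortality model described adjusts for variables some of which can arise after cluster assignment and partly measure or result from the clustered conditions. It may attenuate the cluster-mortality association and does not by itself give prognosis by cluster. The protocol does not allow the amount to be estimated: the 13% to 59% loss in log hazard ratio rests on assumed effect sizes and on treating the covariate as a pure mediator. The ethnicity gap is a contradiction between Sections B and N, with an effect of about 1% to 4% in either direction under the assumptions shown. The death entry is a misclassification to correct. This concerns one secondary outcome of a descriptive study and is a cheap improvement.

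**What to change.** - In Section N, name as the main prognostic model: cluster plus age, sex, ethnicity and IMD, all measured at or before cluster assignment. Risk factors recorded before assignment, such as smoking and BMI, may be added as confounders.
- Keep the planned model, with time-updated clinical measures, utilisation and life events, as a second model labelled as a conditional (explanatory) association.
- Treat ethnicity the same way in Sections B, N and O, whether as covariate or as stratum.
- In Section M, move date and cause of death out of the life events and keep it with the outcomes.

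The cost is a few lines of text and one extra reported model. No new data are needed, and the planned time-dependent analysis is retained.
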